#### **8.7.6. Grading of Adverse Event severity**

Clinical adverse events and laboratory parameters will be graded by investigator using the Common Toxicity Criteria for Adverse Events (CTC AE) version 4 (May 2009) so that comparisons can be made between treatment arms. This specific

adverse event severity grading scale is used in order to standardize reporting between investigators and sites.

In the case that an AE is not listed, the assessment of intensity/severity will be based on the investigator's clinical judgment. The maximum intensity/severity experienced should be recorded and will be assigned to one of the following categories.

- MILD - Does not interfere with patient's usual functions
- MODERATE - Interferes to some extent with patient's usual functions
- SEVERE - Interferes significantly with patient's usual functions

It is to be noted the distinction between severity and seriousness of adverse events. A severe adverse event is not necessarily a serious event.

#### **8.7.7. Adverse Event causality assessment**

For both serious and non-serious adverse events, the investigator is required to assess the possible relationship between the adverse event and the study drug, i.e. to determine whether there exists a reasonable possibility that the study drug caused or contributed to the adverse event. Causality will be listed as not related, unlikely, possible or probable.

To help investigators with the decision binary tree (bullet points below) in the evaluation of causality, the CIOMS VI group recommends that investigators be asked to consider the following before reaching a decision:

- Medical history
- Lack of efficacy/worsening of existing condition
- Study medications
- Other medications (concomitant or previous)
- Withdrawal of study medication, especially following trial discontinuation / end of study medication
- Erroneous treatment with study medication (or concomitant)
- Protocol related procedure

The decision to suspend, and resume treatment or to permanently interrupt treatment due to an adverse event will be left to the clinician in charge. This decision will be taken based on the patients best interests.

#### **8.7.8. Exposure in utero**

All women who are pregnant are to be excluded from this study. This is specifically due to the teratogenic potential of miltefosine (demonstrated in rats). The manufacturer recommends that effective contraception should be used during and up to 3 months after treatment of miltefosine but we will extend it to 4 months according to new available data. However, in the unlikely event that any trial subject becomes or is found to be pregnant while receiving an investigational drug or within 90 days of discontinuing the investigational drugs, the investigator must submit the event on an SAE form. This must be done irrespective of whether an adverse event has occurred. The information submitted should include the anticipated date of delivery. The investigator will follow the subject until completion of the pregnancy or until pregnancy termination (i.e., induced / spontaneous abortion). The investigator will provide pregnancy outcome information as a follow up to the initial SAE form. In the case of a live birth, a pediatrician should assess the infant at the time of birth and submit a report.

### **8.7.9. Adverse event follow up**

All adverse events should be followed until they are resolved or the investigator assesses them as chronic or stable or the subject participation in the trial ends (i.e., until a final report is completed for that subject). In addition, all serious adverse events and those non-serious events assessed by the investigator as possibly related to the investigational drug must continue to be followed even after the subject participation in the trial is over. Such events should be followed until they resolve or until the investigator assesses them as “chronic” or “stable.” Resolution of such events is to be documented on the CRF/SAE form as appropriate.

## **9. Withdrawal criteria**

If a subject withdraws from the study, the reason must be noted on the CRF. If a subject is withdrawn from the study because of a treatment limiting adverse event, thorough efforts should be made to clearly document the outcome.

A subject should be withdrawn from the trial treatment if, in the opinion of the investigator, it is medically necessary and in the best interests of the subject, or if it is the wish of the subject. If a subject does not return for a scheduled visit, every effort should be made to contact the subject. In any circumstance, every effort should be made to document subject outcome, if possible.

If the subject withdraws consent, no further evaluations should be performed and no attempts should be made to collect additional data, with the exception of follow-up safety data on events that occurred prior to the patient withdrawing their consent. Such information should be collected if possible.

All patients who are classified as a treatment failure and who receive extended treatment or rescue treatment will be followed for 12 months.

### **9.1. Rules in case of treatment suspension or interruption**

In the event that treatment is interrupted (e.g. due to an adverse event), the decision to resume treatment will be taken by the site Principal Investigator.

If miltefosine treatment is interrupted for more than 3 days and requires additional VL treatment (other than that described in the protocol) they will be considered a treatment failure for the purposes of the ITT analysis and excluded from the per protocol analysis. If interruption was for 3 or less days, treatment will start again till the complete dose is administered.

### **9.2. Rules for permanently interrupting study treatment**

If a subject is withdrawn from the study before the full course of the treatment is completed, the day 29 procedures should be completed (i.e. parasitology assessment) unless contraindications are present. The physician must make all necessary arrangements to ensure that the subject receives the appropriate treatment for the relevant medical condition (e.g. with drug/s currently recommended

by the national policy).

## 10. Data Analysis and Statistical Methods

### 10.1. Sample size determination

The sample size will be determined according to the sequential design for the primary outcome to be measured at day 29.

Since we are using a sequential approach, the sample size is not defined or known in advance. The maximum sample size needed per arm would be 66 patients (132 total patients) and the maximum analyses performed would be 7 (see Graph 1, upper horizontal axis). The actual sample size may be less than this, with its value depending on the value of the proportion cured.

Graph 1: Triangular region for study arms showing the boundaries for analysing the sequential trial using the Triangular Test, with the following parameters ( $p_0 = 0.75$ ,  $p_a = 0.9$ ,  $\alpha = 0.05$ ,  $\beta = 0.05$  and  $n = 10$ ).

[figure not shown]

### 10.2. Definition of study populations included in the analysis

For the sequential and primary analysis (day 29), an intention to treat (ITT) and per protocol (PP) analysis will be performed.

To take account of missing data, each of the above analysis sets (ITT and PP), the efficacy endpoint will be calculated in two ways:

- complete case analysis: excluding patients with missing efficacy data from estimation of efficacy
- worst case analysis: patients with missing efficacy data will be allocated efficacy results based on their 'worst-case' scenario i.e. treatment failure.

Missing outcome data on the efficacy endpoints could arise if a patient withdraws consent, is lost to follow-up, or has an exam omitted by investigator oversight.

The ITT complete case analysis will be primary.

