| 
Statistics
 
Summary of analysis
 | 
Primary Endpoint Analysis: Day 29
 
The study is designed and will be analysed according to group-sequential methods, specifically the triangular test. The triangular test is one way of analysing group sequential trials and uses straight line stopping boundaries. It involves analysing the data as they accumulate, with points being plotted relative to a triangular region and stopping when the upper or lower boundary of the region is crossed (Graph 1). It has the advantage over other methods of analysing group sequential trials, such as the discrete sequential probability ratio test, in that a closed continuation region is used ensuring that the trial stops within a pre-specified maximum sample size.
 
The type I error rate and power of the study were set to 5% and 95%, respectively (<math>\alpha=0.05</math>, <math>\beta=0.05</math>) with parameters <math>p_0=0.75</math> and <math>p_a=0.90</math>. Based on these specifications, the boundaries of the test were calculated for the null hypothesis, <math>H_0: p \leq p_0</math>, and the alternative hypothesis, <math>H_a: p > p_0</math> (see Graph 1). Based on the rationale above, rejecting the null hypothesis, <math>H_0: p \leq p_0</math>, (crossing the upper boundary) means that we can consider the regimen for compassionate use while failing to reject the null hypothesis (crossing the lower boundary) means that we cannot consider the regimen for compassionate use. Data from each arm will be analysed (for the evaluable patient population or per protocol analysis) after every 10 patients reach the primary endpoint of initial cure, where the actual values of Z and V will be calculated and then plotted on the graph. Depending on where the point falls, that arm of the trial will either continue collecting data for another 10 patients or will stop, concluding with a rejection of the null hypothesis (adequate efficacy) or a non-rejection of the null hypothesis (inadequate efficacy). In the final analysis, asymptotic properties will be used to calculate unbiased estimators of the response rate and its 95% confidence interval taking into account the sequential nature of the analyses.
 
Secondary Endpoint Analysis:
 
When the analyses concludes that an arm should be stopped (i.e. a boundary has been crossed), survival at 1 year will also be evaluated. Due to sequential design employed and the different treatment options to be determined by day 29 outcomes (i.e. repeat treatment and/or pentamidine prophylaxis), subsequent analyses (i.e. the secondary endpoint) are likely to be descriptive only. Such descriptive analyses will focus on survival (alive and disease-free) at 12 months post day 29 assessment and relapses between day 29 and 12 months follow-up, by arm and day 29 outcome.
 
Safety Analysis
 
Adverse events (AEs) will be described on treatment and during follow-up. AEs will be coded using MedDRA and tabulated by severity / CTC V4 AE grading. Causality of AEs will also be tabulated. Serious Adverse Events (SAEs) will be described by individual narratives based on the SAE reports provided by the site investigators. Summary statistics will be tabulated for haematological and biochemical parameters as well as for ART efficacy (CD4 count, viral load) at each time point.
 |

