### **10.6. Efficacy Analysis**

The primary and secondary endpoints have been described in section 2.2.

The primary endpoint (day 29) analysis will be defined as follows:

- Treatment success: absence of parasites on day 29; hence no rescue medication provided up to this time-point.
- Treatment failure: presence of parasites at day 29 *or* requirement of rescue medication due to lack of clinical improvement/ response *or* withdrawn from the study (e.g. due to a treatment limiting adverse event/ patient absconded) *or* death.

The data will be analysed as proportions according to an intention to treat and per protocol analysis for each treatment arm.

The secondary endpoint (12 months post treatment) analysis will be defined as follows:

- Treatment success: treatment success at day 29 or at day 58 in case of extended treatment and patient being alive and disease free (absence of signs and symptoms of VL or if symptomatic, a negative parasitological assessment by tissue aspirate) at day 390.
- Treatment failure: presence of signs of symptoms of VL, confirmed by presence of parasites in a parasitological investigation. It is mandatory that all patients who have possible presence of the disease have a parasitological assessment (a spleen aspirate or a bone marrow aspirate if the spleen is not palpable).

The primary endpoint will be analyzed following Whitehead (1983) including point and interval estimation of the proportion cured in each treatment arm.

Additional analyses will be conducted to evaluate potential differences in response to treatment between relapse versus primary VL cases, and patients that have previous exposure to ART or not. This will be done at the final sequential analysis (when we reach 66 per arm) and after one year follow up. A detailed description will be included in the statistical analysis plan.

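### Sections 10.2 and 10.6 classify patients who leave before the day-29 aspirate differently, and the synopsis names a third population, in a test against a fixed 75% cure rate

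*Protocol*

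**What the plan says.** Protocol Section 10.2 plans ITT and per protocol analyses for the sequential and primary day-29 analysis, each handled in two ways. Complete case means "excluding patients with missing efficacy data from estimation of efficacy". Worst case means "patients with missing efficacy data will be allocated efficacy results based on their 'worst-case' scenario i.e. treatment failure". Missing data "could arise if a patient withdraws consent, is lost to follow-up, or has an exam omitted by investigator oversight". Of these, "The ITT complete case analysis will be primary".

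Section 10.6 defines day-29 failure to include, besides parasites at day 29, need for rescue and death, a patient "withdrawn from the study (e.g. due to a treatment limiting adverse event/ patient absconded".

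The synopsis describes the sequential looks differently: "Data from each arm will be analysed (for the evaluable patient population or per protocol analysis) after every 10 patients reach the primary endpoint".

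Section 9.2 asks that, after withdrawal before the full course is completed, "the day 29 procedures should be completed (i.e. parasitology assessment) unless contraindications are present". Section 9 adds that once consent is withdrawn no further evaluations are made, apart from safety follow-up of events that had already occurred.

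**The concern.** Take a patient who withdraws consent, or absconds, on day 12 and has no aspirate. Section 10.6 makes this patient a failure. Section 10.2 can make the same patient missing and drop them from the primary denominator. The synopsis would drop them from the looks if they are not evaluable or not per protocol. The text ranks none of the three.

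The choice matters because the trial makes no between-arm comparison (Sections 1 and 3.3). Each arm is judged against an absolute 75%, so equal losses in the two arms do not cancel. Removing failures can only move an arm towards the upper boundary, which the synopsis equates with adequate efficacy and consideration for compassionate use.

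**Working it through.** **Inputs.** From the synopsis and Section 10.1: p0 = 0.75, pa = 0.90, α = β = 0.05, groups of 10 per arm, at most 66 patients per arm and 7 analyses. The synopsis states that "The type I error rate and power of the study were set to 5% and 95%, respectively" and tests p ≤ p0 against p > p0. The fraction d without a day-29 result is not in the protocol and is assumed.

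**Reproducing the plan's maximum** (one-sided triangular test with correction for discrete looks):

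- θ = ln[pa(1 − p0) / (p0(1 − pa))] = ln[(0.90 × 0.25)/(0.75 × 0.10)] = ln 3 = 1.0986
- a = (2/θ) ln(1/(2α)) = (2/1.0986) × ln 10 = 4.192
- c = θ/4 = 0.2747
- Information per group = 10 × 0.75 × 0.25 = 1.875; a′ = 4.192 − 0.583 × √1.875 = 3.394
- Maximum n = a′ / (c × 0.1875) = 3.394 / (0.2747 × 0.1875) = 65.9

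This gives 66 patients and 7 looks, as stated. Without the correction the maximum would be 81.4, so the corrected boundaries are the ones to use.

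**Boundaries.** With V = 0.1875n and Z = (cures − 0.75n), an arm stops as adequate if Z ≥ a′ + cV and as inadequate if Z ≤ −a′ + 3cV. Looks are at 10, 20, 30, 40, 50, 60 and 66. The probability of ending as adequate was found by exact binomial enumeration over these looks.

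**Effect of exclusion.** Let s be the success rate under 10.6 and d the fraction excluded, all of them 10.6 failures. The complete case rate is then s/(1 − d). With s = 0.75:

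| Assumed d | Complete case rate | Chance of declaring the arm adequate |
|---|---|---|
| 0 | 75.0% | 4.0% |
| 2% | 0.75/0.98 = 76.5% | 6.6% |
| 3% | 0.75/0.97 = 77.3% | 8.4% |
| 5% | 0.75/0.95 = 78.9% | 13.5% |

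As a count, 50 cures in 66 randomised is 75.8%. If 5 of the 66 withdrew or were lost and are excluded, it becomes 50/61 = 82.0%.

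**Cost of counting them as failures.** If patients with a result cure at 90%, the analysed rate is 0.90(1 − d):

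| Assumed d | Analysed rate | Chance of declaring the arm adequate |
|---|---|---|
| 0 | 90.0% | 0.89 |
| 3% | 87.3% | 0.71 |
| 5% | 85.5% | 0.56 |

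The 0.89 at d = 0, against the stated 95% power, depends on the exact discrete enumeration and on the convention at the last look. It serves only as the reference for this comparison.

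**The case against.** The two sections can be read together. A patient whom 10.6 calls a failure has an outcome, so is not missing, and 10.2 then covers only the remainder. Section 10.6 does not use the terms loss to follow-up or withdrawal of consent, and 10.2 says only that missing data could arise in those ways. This reading is possible, but nothing in the text adopts it. A patient who withdraws consent before day 29 fits both sections, an absconder is in substance lost to follow-up, and the synopsis population agrees with neither section.

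Losses may also be few. Patients are hospitalised for about 30 days (Section 3.2), dosing is given or observed by staff (Section 10.5), and Section 9.2 asks for the aspirate after withdrawal. Section 1 gives a rough anchor from one trial site on a different regimen: cure, death and parasitological failure sum to 74 + 8 + 16 = 98% in primary cases and 36 + 5 + 56 = 97% in relapses. That leaves 2–3% for everything else, which is an inference and not a stated dropout rate. This point stands, and it places the likely effect near the lower rows of the first table. The planned worst case analysis would also reveal a divergence, but it is not primary and no decision is attached to it.

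A reader might infer that the sickest patients would be the ones dropped. The protocol does not support that. Deaths and patients needing rescue are failures under 10.6 and are not on the 10.2 list. The contraindication clause in 9.2 covers only patients already withdrawn. Bone marrow is allowed in place of spleen aspirate when the spleen is not palpable, and at diagnosis also for low platelets, low haemoglobin or bleeding tendency.

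**Conclusion.** The conflict is real and concerns stated rules: one section excludes patients whom another counts as failures, and the synopsis names a third population for the stopping decision. The direction of the effect is certain whenever such patients exist, because s/(1 − d) exceeds s for any d above zero. The size is modest at plausible losses: from 4.0% to about 6.6% or 8.4% at 2% or 3% excluded, against a nominal 5%, and 13.5% at 5%. These figures assume a true 10.6 success rate of exactly 75%, that every excluded patient is a 10.6 failure, and the boundaries reconstructed above. With no missing day-29 results the effect is nil.

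A reader might also carry the formula to 8% or 10% excluded, where the error reaches 26% or 39%. Nothing in the protocol suggests losses on that scale during a supervised inpatient course, so those figures should not describe the problem.

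**What to change.** Reconcile the synopsis, Section 10.2 and Section 10.6 before the first look.

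- Name one population, ITT, for the sequential looks and the final estimate, and replace the synopsis reference to evaluable or per protocol patients.
- State that the 10.6 definition governs that population: patients who withdraw, abscond or are lost before the day-29 aspirate are failures.
- Treat as missing only an aspirate not done in a patient still on study at day 29 who is not otherwise a 10.6 failure.
- Keep the complete case analysis as now worded, and the worst case analysis, as sensitivity analyses.

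The change is one of wording, and the maximum stays at 66 per arm for the stated p0 and pa. The cost is power, and few losses suffice: with 90% cure among patients with a result, counting 3% or 5% as failures lowers the chance of declaring adequacy from about 0.89 to 0.71 or 0.56. The sponsor should therefore confirm that p0 = 0.75 and pa = 0.90 are both meant on the 10.6 definition. If they were set for patients with a day-29 result, they need restating and the boundaries recalculating.

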### **10.3. Subject Disposition**

The number of patients who were screened, failed screening, randomised, completed the treatment period, completed the follow-up, early terminations and reasons for early termination of study will be summarized by number of patients (n) and percentages (%).

### **10.4. Baseline**

The continuous variables of the baseline and demographic characteristics will be summarized using number of patients (n), mean, SD, median, minimum and maximum. The categorical variable gender will be summarized using number of patients (n) and percentage.(%).

### **10.5. Treatment Compliance**

All VL drugs will be directly administered (IV) or be directly observed (oral) by study medical staff. All failures with compliance (e.g. vomiting) will be appropriately documented.

### **10.6. Efficacy Analysis**

The primary and secondary endpoints have been described in section 2.2.

The primary endpoint (day 29) analysis will be defined as follows:

- Treatment success: absence of parasites on day 29; hence no rescue medication provided up to this time-point.
- Treatment failure: presence of parasites at day 29 *or* requirement of rescue medication due to lack of clinical improvement/ response *or* withdrawn from the study (e.g. due to a treatment limiting adverse event/ patient absconded) *or* death.

The data will be analysed as proportions according to an intention to treat and per protocol analysis for each treatment arm.

The secondary endpoint (12 months post treatment) analysis will be defined as follows:

- Treatment success: treatment success at day 29 or at day 58 in case of extended treatment and patient being alive and disease free (absence of signs and symptoms of VL or if symptomatic, a negative parasitological assessment by tissue aspirate) at day 390.
- Treatment failure: presence of signs of symptoms of VL, confirmed by presence of parasites in a parasitological investigation. It is mandatory that all patients who have possible presence of the disease have a parasitological assessment (a spleen aspirate or a bone marrow aspirate if the spleen is not palpable).

The primary endpoint will be analyzed following Whitehead (1983) including point and interval estimation of the proportion cured in each treatment arm.

Additional analyses will be conducted to evaluate potential differences in response to treatment between relapse versus primary VL cases, and patients that have previous exposure to ART or not. This will be done at the final sequential analysis (when we reach 66 per arm) and after one year follow up. A detailed description will be included in the statistical analysis plan.

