The most important problem is treatment; when compared with VL patients who are not infected with HIV, cure rates for HIV co-infected patients are lower, drug toxicity is increased and mortality rates are higher. Relapses are common; studies have shown that most if not all are true relapses with the same leishmania strain although some new infections may also occur. Persistent low CD4 counts may play a role and with each relapse the response to treatment is lower.

The incidence of cases in the Mediterranean area has decreased with the introduction of anti-retroviral therapy (ART); it is probable that ART prevents asymptomatic patients from becoming symptomatic by restoring immunity.

While the epidemic of co-infection has decreased in the Mediterranean area, with further spread of HIV in VL endemic areas, an increase in co-infected cases has been reported in Africa (Ethiopia) and in Latin-America (Brazil).

In Ethiopia the national HIV prevalence is 2.1% (MoH, 2007). VL is reported from at

least 40 areas but 60% of cases occur in the Metema and Humera lowlands. Co-infection rates range from 18-31%. Most patients are young men who are among the 300 - 500,000 migrant workers who come each year from the highlands to work in the agricultural schemes; while some are already infected on arrival, it is assumed that others contract HIV by visiting local sex workers.

In Brazil, the number of VL cases is increasing country-wide as is the number of co-infected patients. This is thought to be related to the increasing urbanization.

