### **2.2.2 Secondary Endpoint(s)**

#### **Relapse-free survival at 12 months as defined as**

The patient being alive and disease free from day 29 (if initially cured) or day 58 (if they received an extended treatment) and remains disease free until the last follow-up assessment (i.e. day 390).

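### The day-390 relapse-free survival endpoint gives death and loss to follow-up no stated category, and its yes/no scoring discards the follow-up of patients lost early

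*Protocol*

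**What the plan says.** Section 2.2.2 names the secondary endpoint relapse-free survival at 12 months and describes it as a course over time: alive and disease-free from day 29, or from day 58 after extended treatment, through day 390.

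Section 10.6 turns this into two categories. Success is "treatment success at day 29 or at day 58 in case of extended treatment and patient being alive and disease free", judged at day 390. Failure is "presence of signs of symptoms of VL, confirmed by presence of parasites in a parasitological investigation". Neither death, loss to follow-up nor rescue treatment appears in that failure definition. In the same section, the day-29 failure definition does list rescue medication, withdrawal and death.

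The only missing-data rules are in section 10.2, which opens "For the sequential and primary analysis (day 29), an intention to treat (ITT) and per protocol (PP) analysis will be performed". It then gives two options: "complete case analysis: excluding patients with missing efficacy data from estimation of efficacy", or "patients with missing efficacy data will be allocated efficacy results based on their 'worst-case' scenario i.e. treatment failure". The explanatory sentence is wider: "Missing outcome data on the efficacy endpoints could arise if a patient withdraws consent, is lost to follow-up".

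The synopsis (Statistics, secondary endpoint analysis) expects the secondary analysis to be descriptive. It covers 12-month survival and relapses by arm and day-29 outcome. No time-to-event estimator is named. The sentence in 10.6 that defers detail to a statistical analysis plan follows the subgroup analyses (primary versus relapse, prior ART).

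**The concern.** Two things looked wrong.

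First, the two categories in 10.6 do not cover everyone. A patient who dies without parasitological confirmation is not a success, because success requires being alive, and is not a failure as defined. A patient lost while well is neither. An analyst would have to choose how to count both groups after seeing the data.

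Second, if the 10.2 rules fill the gap, neither suits a year-long endpoint. Complete case keeps patients whose relapse was seen before they left but drops those who left disease-free, along with all their disease-free time. Worst case counts every loss as a relapse or death. Substantial loss is plausible: of co-infected patients in Ethiopia the background says "Most patients are young men who are among the 300 - 500,000 migrant workers". Section 3.3 calls relapse a major problem in these patients, so the 12-month figure will be read closely even if it is only descriptive.

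**Working it through.** **Figures in the protocol.** None is given for day 390: no expected rate, loss rate or precision. The only design figure is the maximum of 66 per arm for day 29. It reproduces as a one-sided triangular test with p0 = 0.75, pa = 0.90, alpha = beta = 0.05 and groups of 10:
- theta = ln[0.90 × 0.25 / (0.75 × 0.10)] = ln 3 = 1.0986
- a = (2/theta) × ln(1/(2 × 0.05)) = 4.192; c = theta/4 = 0.2747
- discrete-look correction = 0.583 × sqrt(10 × 0.75 × 0.25) = 0.798
- Vmax = (4.192 − 0.798)/0.2747 = 12.36; n = 12.36/0.1875 = 65.9, so 66

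This figure is unaffected by the present point. It is used below only for precision.

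**Assumptions for day 390.** True 12-month relapse-free survival S is 50–80%. The probability L of loss by 12 months, absent an event, is 5–30%. Hazards are constant, with lambda = −ln S and mu = −ln(1 − L).

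**Loss independent of outcome.**
- Seen event-free at 12 months: S(1 − L). This is the worst-case estimate.
- Event seen before loss: E = lambda/(lambda + mu) × [1 − S(1 − L)].
- Complete case: S(1 − L) / [S(1 − L) + E].

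For S = 0.70 and L = 0.20, lambda = 0.357 and mu = 0.223. Worst case = 0.70 × 0.80 = 0.560. E = 0.615 × 0.440 = 0.271. Complete case = 0.560/0.831 = 0.674.

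| L (S = 70%) | Worst case | Complete case |
|---|---|---|
| 5% | 66.5% | 69.4% |
| 10% | 63.0% | 68.8% |
| 20% | 56.0% | 67.4% |
| 30% | 49.0% | 65.8% |

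Over the whole grid the worst-case bias runs from −2.5 to −24 points and the complete-case bias from −0.4 to −5.1 points. Kaplan-Meier recovers S. For scale, the 95% CI half-width at n = 66 and S = 0.70 is 1.96 × sqrt(0.70 × 0.30/66) = 11 points.

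**Loss linked to outcome** (400,000 simulated patients; baseline S = 70%, L = 20%).

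| Scenario | Truth | Kaplan-Meier | Complete case | Worst case |
|---|---|---|---|---|
| Event hazard 4 times higher after loss | 64.4% | 69.9% | 67.4% | 56.0% |
| Loss hazard tenfold in the 2 months before an event | 70% | 76.7% | 73.4% | 55.6% |
| Event hazard halved after loss | 71.5% | 70.1% | 67.5% | 56.1% |

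In the first two rows complete case and Kaplan-Meier are both too high, Kaplan-Meier more so, and the truth lies between Kaplan-Meier and worst case. In the third row both are too low.

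**Unequal follow-up.** Day 29 to day 390 is 361 days and day 58 to day 390 is 332 days. Section 8.1 allows the last visit to vary by two months either way. A single status at day 390 therefore mixes different times at risk.

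**The case against.** The strongest reply is that this is an estimator preference for a secondary, descriptive endpoint. The definition in 2.2.2 is compatible with Kaplan-Meier, and a statistical analysis plan that is not at hand may specify it. That stands in part: the absence of the words Kaplan-Meier is not itself an error. It does not answer the gap in 10.6, which states the outcome categories itself and leaves death and loss out of them.

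Four stronger readings may tempt a reader, and the documents do not support them:
- *That the protocol drops or fails every patient lost before day 390.* Section 10.2 introduces its rules for the sequential and day-29 analysis. The plural wording about efficacy endpoints makes wider use plausible but does not state it.
- *That both rules must bias the result downward.* Only worst case is certain not to overstate. Complete case can go either way, and its bias is small at low loss: 1.2 points at 10% loss with S = 70%.
- *That Kaplan-Meier is unbiased here.* It needs loss unrelated to outcome, which is doubtful in a mobile and very ill population. Relapse times are also interval-censored: visits are at day 58 (86), 210 and 390, and aspirates in follow-up are done only when clinically indicated (8.3). Monthly prophylaxis visits (7.8) narrow the intervals only for patients who receive it.
- *That all the dates needed are already collected.* Visit dates are (12.3). But from one month after treatment stops, only serious events in patients on prophylaxis are reported (8.7.4). Late deaths off prophylaxis depend on the general instruction in section 9 to document outcomes.

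Nor is this the only long-term result, since the synopsis also plans to describe relapses between day 29 and 12 months.

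**Conclusion.** The concern holds in a limited form. The day-390 failure definition in 10.6 is incomplete: death without confirmed VL and loss to follow-up have no category, and rescue is not listed although section 7.9 makes it a failure. The yes/no scoring also makes no use of the disease-free time of patients lost early.

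If the 10.2 rules are carried over, worst case understates relapse-free survival in proportion to loss: by 7 points at 10% loss and 14 at 20% when the true value is 70%, the latter larger than the 11-point half-width at 66 per arm. Complete case is about 1 to 3 points low at the same losses if loss is independent of outcome, and of uncertain direction otherwise. These sizes rest on assumed loss rates, assumed relapse-free survival and constant hazards. The primary day-29 analysis and its sample size are not affected.

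**What to change.** In section 10.6:
- Define the events for the 12-month endpoint as death, parasitologically confirmed relapse, failure to clear parasites by the day 29/58 assessment, and receipt of rescue medication (already a failure under 7.9).
- Add a per-arm Kaplan-Meier or interval-censored estimate of 12-month relapse-free survival with its 95% CI.
- State one time origin. Day 29 would match the synopsis, which counts 12 months from that assessment. Enter never-cleared patients as events at the origin.
- Censor at the last visit documented disease-free.
- Keep the day-390 proportion and the worst case as sensitivity analyses, and say in 10.2 which missing-data rules apply at day 390.

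Record vital status at day 390 for all patients, including those not on prophylaxis.

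The analysis changes cost only wording. Vital status, and the date of relapse detection if the case report form lacks it, would be a small addition to data collection. The drawback is that the new estimate may be too high if patients leave because they are relapsing or dying, so it should always appear next to the worst case.
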